### Statistical analysis

*Sample size.* For the primary endpoint, we computed an appropriate sample size based on an interventional study [55] in older adults with SCD that measured the same cognitive outcome as our study. In that study, a change of 6.8 points in the R-BANS score was observed in the treatment group (baseline mean = 95.9, standard deviation SD = 11.1; posttreatment mean = 102.7, SD = 9.9). To compute the sample size of our study, the following hypotheses were made: i) an SD at baseline equal to 11 in both study groups (treatment and placebo); ii) a correlation between baseline-post treatment of the R-BANS values of 0.7, corresponding to an SD of about 8.5; iii) a change in the placebo group (precautionary hypothesis) of 20% with respect to the change in treatment group (i.e., a change of 1.4 points in the R-BANS score in the placebo arm). Under these hypotheses, by using a two-tailed t test with a significance level alpha = 0.05 and a power of 0.8, the minimum appropriate sample size for detecting a significant difference between the pre-post changes in the two groups was *N* = 80 (40 placebo vs. 40 treated).

For the secondary endpoint, we computed an appropriate sample size based on a study by Sanchez-Rodriguez et al. [56] who measured the biological effect of a nutraceutical in heathy adults. In that study, a mean pre-post difference of 0.2 points was found in IL-8 levels (mean: 1.6 pg/mL (SD = 0.8) vs 1.4 pg/mL (SD = 0.8)). As the duration of the intervention in our study will be longer (36 vs. 3 weeks), we assumed a mean change twice as large as that in their study (0.4 points). Given a two-tailed nonparametric Wilcoxon rank test for matched pairs, an alpha level = 0.05, power = 0.8 and a pre-post correlation of 0.8, an effect size of 0.65 was found. To detect a significant result with a similar effect size, a sample size of *n* = 22 subjects per group (22 treated vs. 22 untreated) was necessary. We therefore set the sample size to *n* = 60 (30 per arm) considering it a good trade-off between cost feasibility and statistical power.

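### The IL-8 sample size is a one-group before-after calculation presented as treated versus untreated, and its effect size does not follow from its stated inputs

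*Protocol article*

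**What the plan says.** In the Protocol article, Statistical analysis, the sample size paragraph for the secondary endpoint starts from a published nutraceutical study in healthy adults. That study had IL-8 means of 1.6 and 1.4 pg/mL, each with SD 0.8. The 0.2 difference is doubled to 0.4 because this trial lasts longer. The test and the remaining inputs are given as "Given a two-tailed nonparametric Wilcoxon rank test for matched pairs, an alpha level = 0.05, power = 0.8 and a pre-post correlation of 0.8".

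From these inputs, "an effect size of 0.65 was found", and the conclusion is that "22 subjects per group (22 treated vs. 22 untreated) was necessary". The blood subsample is then set at 60 (30 per arm), "considering it a good trade-off between cost feasibility and statistical power". No power is given for 30 per arm, and no change in the placebo arm is mentioned for IL-8.

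The R-BANS calculation just before it is built differently. It uses a two-tailed t test on the difference between the two groups' changes and assumes that the placebo group changes by 20% of the treated group's change.

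**The concern.** The trial is randomised and placebo-controlled, and its secondary aim is the effect of the treatment on blood biomarkers. The IL-8 question is therefore treatment against placebo. A matched-pairs test answers a different question, namely whether IL-8 moved within one group. It uses the variance of one group's change and leaves out the second arm's variance and mean change. Labelling its result as treated versus untreated makes a one-group number look like a two-arm number.

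The two adjacent calculations show the conflict. At the same alpha and power, R-BANS has an effect size of about 0.635 and needs 40 per arm, while IL-8 at 0.65 is said to need 22. Both cannot be right for a two-arm comparison.

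Separately, 0.65 does not come out of the change, SD and correlation printed beside it. Since 60 is derived from the 22, a reader who sees 30 as comfortably above 22 would assume more than 80% power without knowing which assumptions that needs.

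**Working it through.** **Inputs** (all from the Sample size paragraphs): change 0.4; SD 0.8 at both times; pre-post correlation 0.8; stated effect size 0.65; two-sided alpha 0.05; power 0.80; 22 per group stated; 30 per arm chosen. Normal data are assumed. Rank tests are approximated by multiplying n by 3/π, their efficiency relative to the t test for normal data.

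**1. Reproducing the 22.** A one-group matched-pairs Wilcoxon test at 0.65 has power 0.789 with 21 pairs and 0.809 with 22 (0.802 by simulation). So 22 is the number of pairs in one group.

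**2. The effect size.** SD of change = 0.8 × √(2 × (1 − r)).
- r = 0.8: SD of change = 0.8 × √0.4 = 0.506, and 0.4 / 0.506 = 0.79
- r = 0.7: SD of change = 0.8 × √0.6 = 0.620, and 0.4 / 0.620 = 0.645, or about 0.65

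The stated inputs give 0.79. At 0.79 the matched-pairs test needs 16 pairs, not 22, so this slip taken alone is conservative.

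**3. The two-arm comparison.** The effect size is now the between-arm difference in mean change divided by the SD of change. With no placebo change (an assumption), the difference is still 0.4. Ranges run from the rank test to the t test.

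| Effect size | n per arm for 80% power (t / rank) | Power, 22 per arm | Power, 30 per arm |
|---|---|---|---|
| 0.65 | 39 / 40 | 0.54–0.56 | 0.68–0.70 |
| 0.79 | 27 / 28 | 0.71–0.73 | 0.84–0.85 |

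Simulated rank-test power agrees: 0.537 and 0.674 at 0.65, and 0.701 and 0.832 at 0.79, for 22 and 30 per arm.

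**4. Cross-check with R-BANS.** (6.8 − 1.4) / 8.5 = 0.635. A two-sample t test with 40 per arm has power 0.801, so the primary calculation holds as a two-arm calculation.

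**5. Sensitivity at 30 per arm.**
- *Placebo changes by 20% of the treated change*, as assumed for R-BANS: the effect sizes become 0.65 × 0.8 = 0.52 and 0.79 × 0.8 = 0.63, with power 0.49–0.51 and 0.65–0.67.
- *Baseline-adjusted comparison, no placebo change:* residual SD = 0.8 × √(1 − r²). At r = 0.7 the effect size is 0.4 / (0.8 × √0.51) = 0.70 and power is about 0.76. At r = 0.8 it is 0.4 / (0.8 × 0.6) = 0.83 and power is about 0.89.

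**The case against.** The strongest reply is that nobody will run the trial with 22 per arm for bloods. The plan sets 30 per arm and claims no power for it. If the printed correlation of 0.8 is right and placebo does not change, 30 per arm gives 0.84–0.85 between arms, and a baseline-adjusted analysis would give about 0.89. The planned analysis is a mixed model, not the sizing test, and whether it adjusts for baseline may be settled in an analysis plan that is not shown. All of this stands, and it limits the consequence. It does not rescue the text, which attaches 80% power to 22 treated versus 22 untreated. That is false between arms at either effect size.

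Other points also stand:
- The 20% placebo change was a precautionary assumption for R-BANS, a repeated cognitive test for which the article itself anticipates learning. Nothing in the article says that a blood cytokine should behave in the same way, so for IL-8 it is a sensitivity case only.
- A correlation of 0.7 is the simplest source of 0.65 but not the only one. At correlation 0.8, an unrounded change near 0.35 with SD near 0.85 gives 0.35 / (0.85 × √0.4) = 0.65. That lies at the edge of what rounding allows, and the article does not state it.
- The article calls the trial a pilot and describes it as exploratory.

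A reader might infer that IL-8 is underpowered at 30 per arm, or that a null result would be taken as conclusive. The documents support neither. The first depends on which input is the mistaken one, which they do not settle. On the second they say nothing.

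**Conclusion.** The concern holds as an error in a stated calculation. The 22 is a one-group number labelled as a two-arm number, and 0.65 contradicts the change, SD and correlation given with it. Between arms, 22 per arm gives 0.54–0.56 power at 0.65 and 0.71–0.73 at 0.79, against the stated 0.80.

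For the planned 30 per arm, the answer lies between about 0.68 and 0.85 with no placebo change, depending on whether the effect size or the correlation is the misprint. These figures rest on normally distributed changes, equal SDs in both arms and complete data.

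Because the endpoint is secondary, no power is claimed for the chosen size, and one of the two readings exceeds 80%, this is a correction that should be made but not a must-fix.

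**What to change.** Replace the IL-8 paragraph with a two-sample calculation on the between-arm difference in IL-8 change:
- Reconcile the correlation with the effect size: 0.7 with 0.65, or 0.8 with 0.79.
- State what change is assumed in the placebo arm.
- Keep 60 participants and report the power of 30 per arm on the chosen inputs: about 0.68–0.70 or 0.84–0.85 with no placebo change.
- Optionally add the 20% placebo change as a labelled sensitivity case (0.49–0.51 or 0.65–0.67).
- If the IL-8 comparison is to be baseline-adjusted, say so and give the matching power (about 0.76 or 0.89 with no placebo change).

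The cost is rewriting one paragraph. No participants or assays are added. Whether the reported power falls below 80% depends on which inputs the authors confirm.

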## Discussion

This article presents the rationale and methods for a pilot clinical trial on the cognitive and biological effects of citrus peel extract standardized in levels of AUR and NAR on older adults with SCD. Currently, limited treatments are available for elderly individuals reporting SCD who are potentially at risk of developing cognitive impairment and dementia. Therefore, it is important to test the efficacy of interventions that may promote cognitive health and ultimately prevent cognitive decline [7].

The nutraceuticals have shown promise in cognitive enhancement, but only a few randomized clinical trials have evaluated their effect on SCD. In a recent systematic review of the effects of nutrition on cognitive function in healthy adults, only 6 out of 48 interventions with dietary supplements were carried out on subjects with SCD [57]. Of these 6 studies, only one evaluated the effect of a long-term (24 weeks) intervention in older adults with SCD defined according to the international criteria [31]. In half of these 6 studies, concerns have been raised about quality. Last, although antioxidant and anti-inflammatory properties have been recognized as the potential mechanisms linking dietary supplements with cognitive functions, none of six studies included biological biomarkers as surrogate outcomes of efficacy. Our pilot clinical trial overcame these limitations and will provide preliminary evidence in the emerging field of using dietary interventions for SCD.

The primary endpoint of the trial is the R-BANS total score. The R-BANS is a well-established clinical tool that was specifically designed for diagnosis, tracking, and clinical trial outcome measurement in early and prodromal AD [58]. Additionally, the R-BANS is one of the cognitive measures recommended for drug trials and research on preclinical AD [59]. The other cognitive outcome measures included in the trial were cognitive tests sensitive to ageing and early dementia. In particular, the California Verbal Learning, Trail Making, and Clock Drawing tests have been used in AD prevention trials [60]. The Stroop test, attentional matrices, and Wisconsin Card Sorting test have been administered in studies of nondemented older adults [61, 62] and SCD [63].

Regarding the self-reported SCD measures, consensus about which questionnaires should be used is lacking [64]. We decided to adopt the Everyday Memory Questionnaire because we found it to be a reliable indicator of subjective memory complaints in older adults [53] and in subjects with SCD [65]. The other questionnaire, Multifactorial Memory, was an Italian version with robust psychometric properties, ensuring comparability among studies in different countries. Moreover, it specifically taps metamemory, i.e., knowledge about one’s own memory, which is a sensitive measure of SCD intervention efficacy [7],

The secondary endpoint of the trial is the change in IL-8 levels. The IL-8 is a proinflammatory cytokine that can contribute to the pathophysiology of AD [66, 67]. A study showed that elevated IL-8 levels were associated with worse memory and cognitive speed in healthy elderly individuals [68], suggesting its potential role as a surrogate biological marker of early cognitive dysfunction. As experimental studies have shown that AUR and NAR decrease IL-8 levels [69, 70], we believed that levels of this cytokine were an appropriate method of evaluating the biological effect of citrus phytochemicals in cognitively frail elderly individuals. The other biological outcome measures were related to biological pathways linking dietary interventions with cognitive function improvement. Due to financial constraints, we selected a small, but representative panel of biomarkers indicative of pathways that benefit from AUR and NAR. They included levels of brain-derived neurotrophic factor and insulin-like growth factor-1 [71, 72], nitric oxide, thiobarbituric acid reactive substances, and superoxide dismutase [71, 73], and pro- and anti-inflammatory molecules and cytokines [74, 75]. In addition, we included neurofilament light chain because this protein is becoming increasingly valuable as a peripheral biomarker of neuronal damage and subjective cognitive decline [76].

We used citrus peels as the source of the nutraceutical administered in the trial because they are among the richest natural sources of AUR and NAR [77, 78]. Thanks to favourable climatic and geographical conditions in southern Italy—the region from which the lemons used in this study originated—*Citrus* plants are easily grown. This would allow for large-scale in-house production of the nutraceutical under study. As multiple phytochemicals work synergistically with each other to produce cognitive benefits [12], we decided to manufacture the nutraceutical using the whole citrus peel extract instead of the individual phytochemicals. However, we conducted a complete chemical characterization of the whole extract to allow result comparison of our results with those of other studies.

We established the trial nutraceutical dosage based on estimated data of flavonoid intake and major food sources of the elderly individuals [79]. Even though these estimations may be subject to methodological limitations, such as overlooking individual bioavailability and metabolism in the human body, they provide a basis to study the effect of dietary supplementation in reducing the risks of chronic diseases in healthy people [80]. In particular, our trial nutraceutical provided approximately 60 mg/day of total flavonoids, which is equal to or greater then the flavonoid intake estimated in elderly individuals according to analysis of food samples or food tables [79]. The selection of a placebo-only control group as a comparator was justified because no interventions are available for SCD.

The health risks of the studied citrus phytochemicals are expected to be minimal. No side effects of AUR administration in animal models [81] or in older adults [29] have been reported. A recent randomized clinical trial that administered NAR to healthy adults showed no relevant adverse events or changes in blood safety markers [82]. Possible side effects of citrus phytochemicals will be monitored.

We designed the trial following the recommendations of the International Academy on Nutrition and Ageing Task Force for trials of nutritional interventions to slow cognitive decline in older adults [34]. Accordingly, our target population was represented by frail elderly individuals, i.e., subjects with SCD, who are at increased risk of cognitive decline. Although SCD alone is not sufficient to identify preclinical AD in the absence of AD biomarkers, we included older adults with characteristics of SCD *plus*, which are associated with an increased likelihood of underlying AD pathology [83]. Second, the length of the trial was 36 weeks, which is a longer treatment period than that of other studies of nutraceuticals for SCD. As small cognitive effects have been shown in trials lasting from 8 to 24 weeks [84, 85, 86, 87, 88], we expect that a longer trial period, including midpoint testing, will provide more information on the trajectory of cognitive changes. Last, the inclusion of biological markers will provide surrogate measures of treatment efficacy and allow us to identify possible mechanisms of action underlying the proposed treatment-associated benefits on cognition, as recommended for AD drug development [89].

### Limitations

A limitation of the study is the lack of genetic (apolipoprotein E, *APOE* gene) and biological (AD biomarkers) characterizations in our trial population. In particular, the *APOE4* allele is the major genetic risk factor for AD and can influence the rate of cognitive decline in SCD subjects [90]. The exploratory nature of our study prevented equal allocation of participants into study groups according to the *APOE4* allele and the provision of a biological AD signature of the participants.

## Conclusions

Positive results from this study will inform the design of larger clinical trials of longer duration to test citrus phytochemicals supplementation as a strategy for AD prevention and will allow the public health organizations to plan interventions for at-risk older individuals.

## Data Availability

Not applicable.

## Abbreviations

AD: Alzheimer’s disease
SCD: Subjective cognitive decline
NAR: Naringenin
AUR: Auraptene
LANE: Lab Alzheimer’s Neuroimaging and Epidemiology
R-BANS: Repeatable Battery for the Assessment of Neuropsychological Status
IL-8: interleukin-8
*APOE*: apolipoprotein E
